### Assessment

Each participant will be assessed by an independent trained blinded assessor who is unaware of group allocation.

Assessments with the following standardised and validated outcome measures will be undertaken on three separate occasions; at baseline before the intervention (0 weeks), after the intervention (12 weeks) and at follow-up one month after completion of the intervention phase (16 weeks).

#### Demographic and diagnostic baseline data

Demographic (age, gender) and diagnostic (type of MS, number of years since first symptoms, number of years since diagnosis) data will be collected for all participants on a standardised data collection form. In addition details of current medications will be collected, and any changes to these (or other medical interventions) will be noted throughout the course of the study.

#### Outcome measures

Measures will be undertaken in a standardised order to account for practice and fatigue effects. Comfortable shoes and orthoses/walking aids will be worn, which will be the same on each testing occasion. In all timed tests a stop watch accurate to one decimal place will be used.

All of these measures were used in the case series study [5]. All have demonstrated to be easily administered and clinically relevant. All have published data concerning their psychometric properties, demonstrating them to be valid, reliable and responsive in similar MS samples and with similar interventions. This range of measures reflects the differing aspects of mobility and balance that can be affected in MS, which include speed of walking, ability to maintain balance with variations in base of support, confidence with balance, and self-perception of walking ability.

#### Primary clinical outcome measure

1 10 metre timed walk test [13] - this clinician based measure of mobility will be used to assess speed of walking. In line with other studies of ambulant individuals with MS, a single test will be performed at self-selected speed, from a still start.

#### Secondary clinical outcome measures

1 MS 12 item walking scale [14] - this patient based self-report scale of mobility will be used to assess patient perspective on mobility.

2 Functional Reach - forwards and lateral [15].

Functional reach mirrors the everyday activity of reaching for objects beyond arm's length. In line with other MS studies three trials of each test will be performed and the mean determined.

3 Numerical Rating Scale (10 point) to determine "Difficulty in carrying a drink when walking". This was identified as a common functional difficulty by the site therapists in the case series study [1].

4 Activities-specific Balance Confidence (ABC) Scale [16]

This self-report scale rates the persons perceived level of confidence in performing 16 daily activities.

#### Compliance data

Attendance at training sessions will be recorded for all participants. At each training session, therapists will record specifics in relation to the type, level and repetition of exercises undertaken (Interventions A and B), and duration and content (Control Intervention).

All participants will be asked to complete a tick-box diary to record compliance with their home exercise programme. In the case of interventions A and B, this will also include the number of repetitions undertaken.

#### Measures to explore the underlying mechanisms of change

In addition to the clinically based functional outcome measures, in a sub-group of 20 subjects based at Plymouth University, automatic activation of the deep abdominal core stabilising muscles using ultrasound imaging will be measured before (0 weeks) and immediately after completion of the intervention programme (12 weeks). Measurement of abdominal muscle thickness changes during exercise have been shown to be valid measures of muscle activity [17,18]. Measuring both the resting thickness and thickness upon muscle activation in the transversus abdominus and internal oblique muscles will allow us to determine whether differences in the outcomes of the three interventions exist at an impairment level. This will provide important information pertaining to the mechanisms underlying any functional changes which may be observed to occur.

Current literature suggests that 20 hours training are needed to ensure the acquisition and measurement of ultrasound images is reliable for this purpose [19]. Following 20 hours of training, an intra-rater reliability study will be undertaken to establish reliability of ultrasound measurements on repeated testing. A standardised protocol will be used for image acquisition. Images for each of the first 20 consecutive participants at Plymouth University will be taken before and after the intervention period. Participants will be imaged in supine, both at rest and with an active straight leg raise of their strongest leg to automatically activate the deep abdominal muscles [17]. The ultrasound transducer will be placed on the mid axillary line in between the 12^th ^rib and iliac crest on the contralateral side to the leg being lifted. Participants will lie in supine with arms crossed resting on their chest. An image clip will be taken during quiet respiration (image at rest) and then a command will be given to lift the contralateral leg 5 cm at which time a further image clip will be recorded (image of automatic muscle activation). This procedure will be repeated 3 times. The ultrasound image clips will be transferred to a computer and analysed off-line, where the thickness of the transversus abdominus and internal oblique muscles will be measured as a measure of muscle size and activity during both quiet respiration and automatic activation [17].

### Statistical analyses

Statistical analyses will be undertaken using SPSS version 19.0 (SPSS Corp, Chicago, Illinois, USA). Demographic and diagnostic characteristics and baseline data will be summarised by descriptive statistics.

#### Analysis of primary clinical outcomes

The primary analysis will be an intention to treat comparison of the treatment assigned at randomisation. For each of the two primary outcomes, the treatment effect will be tested and presented at the two-tailed 5% level with no adjustment of multiple testing. Treatment effectiveness will be assessed in terms of the difference in change (follow-up minus baseline) for the following comparisons:

• Pilates based intervention versus relaxation (control)

• Standardized exercise programme versus relaxation (control)

• Pilates based intervention versus standardized exercise programme

Ninety five per cent confidence intervals will be produced for the treatment effect on the primary outcomes. Estimates of treatment effects and their standard errors will be tabulated.

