### Sample size

The sample size for this study is based on data from the case series study investigating the effectiveness of a Pilates based core stability training programme on balance and mobility in a similar sample of people with MS [1]. Based on this data, 30 people in each group is required to detect a 20% change in score on the primary outcome (the 10 metre timed walk 10MTW), with a power = 0.85 and α = 0.05. A 20% change in the 10MTW has demonstrated to be clinically significant in similar samples [11]. To allow for a 10% drop-out rate 100 participants will be recruited for this study.

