### Participant recruitment and group allocation

The Lanarkshire, Newton Abbot and London centres will each recruit 20 participants, and the Plymouth centre will recruit 40 participants.

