#### Participants will be recruited via either

i the physiotherapy department at each of the participating NHS centres, or

ii the SWIMS (South West Impact of MS) database in the case of participants living in the Devon region. SWIMS is a population - based database in which longitudinal data is being collected to assess the impact of MS on over 1100 people in Devon and Cornwall, UK. It is run by the Clinical Neurology Research Group, Peninsula Medical School, Universities of Exeter and Plymouth. Potential participants recruited via this avenue will be made aware of this study in two ways; either by an advertisement placed in the twice yearly newsletter which is sent by the SWIMS team to people with MS who are registered on the database; or via a letter of invitation by the Chief Investigator of SWIMS to participants meeting the inclusion criteria. In either case, the study team contact details will be provided to enable interested SWIMS participants to find out more about the study or in taking part. Under the Data Protection Act, the SWIMS team will not pass on any information about SWIMS participants to the core stability study team. It is only once the core stability team have been contacted by the potential participant that they will begin the recruitment and consent process.

Interested participants will be provided with an information pack describing the study; this will be supported by verbal information when requested. Participants will be screened for eligibility by the principal investigators at each site, who will gain written informed consent for those who meet the inclusion criteria.

After consenting to participate and before intervention, participants will be randomised by the principal investigators at each site to one of three groups -intervention A (Pilates based core stability training), intervention B (standardised physiotherapy exercises) or control intervention C (relaxation). A block randomisation procedure (whereby each site is the block) will be used with central concealment through the use of numbered tickets placed in sealed opaque envelopes, organised by the study co-ordinator. The investigators will open the sealed envelopes sequentially and only after the participant's name and other details are written on the appropriate envelope.

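### The primary analysis is defined as a difference in change from baseline with no stated adjustment for baseline 10 metre walk time or centre; a baseline- and centre-adjusted model would be more precise at small cost

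*Protocol article*

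**What the plan says.** Under Analysis of primary clinical outcomes, the protocol article plans an intention-to-treat comparison and defines the effect measure: "Treatment effectiveness will be assessed in terms of the difference in change (follow-up minus baseline". Three pairwise comparisons follow (Pilates against relaxation, standardised exercise against relaxation, Pilates against standardised exercise), each with a 95% confidence interval. On testing it says that "the treatment effect will be tested and presented at the two-tailed 5% level with no adjustment of multiple testing". It names no model, baseline covariate or centre term.

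Two other sections matter here:

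- **Baseline is available.** Under Assessment, outcomes are measured "at baseline before the intervention (0 weeks), after the intervention (12 weeks) and at follow-up one month after completion".
- **Site restricts the randomisation.** Under Participant recruitment and group allocation, "A block randomisation procedure (whereby each site is the block) will be used". The site targets are: "The Lanarkshire, Newton Abbot and London centres will each recruit 20 participants, and the Plymouth centre will recruit 40 participants".

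Under Sample size, "30 people in each group is required to detect a 20% change in score on the primary outcome", "with a power = 0.85 and α = 0.05". No standard deviation, baseline mean or baseline to follow-up correlation is given.

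**The concern.** Subtracting baseline from follow-up forces the baseline slope to be 1. With equal variances at the two visits, the slope that minimises the variance is the correlation between them, which is below 1. A simple change score therefore over-corrects for baseline. If one arm happens to start slower, regression to the mean makes it appear to improve more.

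Three features of this trial make that relevant. Entry covers EDSS 4.0 to 6.5, with or without a walking aid, so starting times may vary widely. The primary outcome is a single walk per visit, whereas functional reach is averaged over three trials, and single-trial error lowers the correlation. The arms are also small, so chance imbalance is to be expected.

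Site acts as a stratification factor. If sites differ in how much participants change, leaving site out of the analysis tends to make standard errors too wide. At stake is some power, and an estimate that depends on the luck of the baseline draw.

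**Working it through.** **1. The plan's own figures.** Three arms of 30 give 90, and 90/(1 − 0.10) = 100, which reproduces the recruitment target. The 30 per arm cannot be reproduced because no standard deviation is given. Solving backwards with two-sided α = 0.05 and power 0.85, the implied standardised difference is

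d = (1.960 + 1.036) × √(2/30) = 0.774 (normal approximation; 0.787 with the t distribution).

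**2. Assumptions not in the document.** The 85% power is taken to refer to change scores. Variances at baseline and follow-up are equal (s²). The correlation ρ is unknown and is shown over a range, with 0.7 to 0.9 as the main range. 30 per arm are analysed.

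**3. Variance.**

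- Change score: 2s²(1 − ρ)
- Baseline-adjusted: s²(1 − ρ²)
- Ratio: (1 + ρ)/2

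**4. Power at 30 per arm.** Power = Φ(2.996/√ratio − 1.960). For ρ = 0.7: 2.996/√0.85 = 3.250, less 1.960 = 1.290, so power is 0.901.

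| ρ | Variance ratio | Reduction | Change-score n per arm that would match (30/ratio) | Power, normal | Power, t with 83 df |
|---|---|---|---|---|---|
| 0.5 | 0.75 | 25% | 40 | 0.933 | 0.928 |
| 0.7 | 0.85 | 15% | 35 | 0.901 | 0.895 |
| 0.8 | 0.90 | 10% | 33 | 0.885 | 0.877 |
| 0.9 | 0.95 | 5% | 32 | 0.867 | 0.860 |

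The change-score starting points are 0.850 (normal) and 0.842 (t, 87 df). The t column uses d = 0.774.

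**5. Chance imbalance.** The standard error of a baseline difference between two arms is √(2/30) = 0.258 SD. An imbalance of that size shifts the change-score contrast by (1 − ρ) × 0.258 SD. The implied detectable effect is 0.774 × √(2(1 − ρ)) SD.

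| ρ | Shift (SD) | Detectable effect (SD) | Shift as share of effect |
|---|---|---|---|
| 0.5 | 0.129 | 0.774 | 17% |
| 0.7 | 0.077 | 0.599 | 13% |
| 0.8 | 0.052 | 0.489 | 11% |
| 0.9 | 0.026 | 0.346 | 7% |

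**6. Cost.** Baseline uses one degree of freedom and four centres use three, so error degrees of freedom fall from 90 − 3 = 87 to 83. The critical t moves from 1.9876 to 1.9890. Estimating the baseline slope also inflates the expected variance by about 1 + 1/85 = 1.012. The ratios 0.85, 0.90 and 0.95 become 0.860, 0.911 and 0.961.

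**7. Centre alone.** If centre explains 0%, 5% or 10% of the variance of change, t-based power is 84.2%, 86.0% or 87.7%, against 84.2% without the term. None of the site targets (20, 20, 20, 40) divides by three, so arms cannot be exactly equal within a site, but blocking keeps them close.

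**The case against.** The strongest reply is that the text does not exclude adjustment. Regressing change on arm and baseline gives the same treatment coefficient and standard error as regressing follow-up on arm and baseline, so an adjusted difference in change fits the wording. A condensed article often leaves covariates to an analysis plan. This stands: a reader might infer that the plan ignores centre, or commits to raw change scores, but the article only fails to name a covariate. What remains is that the stated effect measure, read plainly, is the unadjusted one. The same article does name a model for the ultrasound data.

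A reader might also infer that the planned comparison is biased. It is not. Under randomisation the unadjusted change score is unbiased on average, and omitting a stratification factor errs towards conservatism. The shifts in the working are conditional on the imbalance that happens to occur.

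Nor is adjustment free, or its gain certain. The gain shrinks as ρ approaches 1. Change scores already remove stable differences between centres in walking time, so a centre term helps only if centres differ in change, and the document gives no evidence of that. Site blocking already limits centre imbalance. If the 85% was computed for change scores, the planned power is kept without any adjustment. All these points stand, and they limit the size of the concern.

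**Conclusion.** The point holds as a recommendation on precision and clarity. The article fixes the primary effect as a difference in change and names neither baseline nor centre, when both are available and one restricts the randomisation. For ρ between 0.7 and 0.9, baseline adjustment cuts the variance by 15% to 5% and lifts power from 0.85 to about 0.90 to 0.87. It also removes a conditional shift of roughly 13% to 7% of the implied detectable effect for a baseline imbalance of one standard error. These sizes rest on an assumed ρ, equal variances, and the premise that the stated power refers to change scores; the document supports none of the three directly. The direction does not depend on the exact ρ: in large samples, baseline adjustment in a randomised comparison is never less efficient than a simple change score. The case for centre is weaker. It is sound practice because site restricts the randomisation, but leaving it out does little harm unless centres differ in change.

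**What to change.** In Analysis of primary clinical outcomes, state that the 10 metre timed walk at follow-up (or, equivalently, its change) will be analysed in one linear model with arm, baseline 10 metre timed walk and centre (four levels), using all three arms. Report the three adjusted pairwise differences with 95% confidence intervals. The sentence should name the visit it applies to, since both 12 and 16 weeks are assessed. If an unadjusted comparison is really intended, say so explicitly.

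The cost is a change of wording and about four of 87 error degrees of freedom. No new data, participants or visits are needed. Fixing the model in advance also rules out a later choice between adjusted and unadjusted results.

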## Background

People with MS frequently experience disabling balance and mobility impairments. One component of balance is postural stability of the trunk. This is now commonly termed "core stability" [1]. People with MS have been found to have reduced trunk stability during arm movements in sitting compared to healthy subjects, implying reduced core stability [2].

Pilates based core stability training is a precise, controlled form of exercise using the stabilising muscles of the body [3]. Despite a lack of scientific evidence to support the effectiveness of core stability training in people with MS, it is increasingly being advocated as a treatment strategy. As a consequence core stability training is often integrated into rehabilitation programmes, both on an individual and group basis. Furthermore Pilates based exercise classes are popular with people with MS who pay to participate in these within community leisure settings.

In response to this, the Therapists in Multiple Sclerosis (TiMS) Research Group based in the United Kingdom (UK) [4], undertook a small scale multi-centre series of eight replicated single case studies (ABA design), across five geographically dispersed centres, to explore the effect of Pilates based core stability training on balance, mobility, and balance confidence in ambulant individuals with MS [5]. Visual analysis (trend, level and slope between baseline and intervention phases), together with the 2 standard deviation band statistical analyses showed improvement in at least 6 of the 9 measures for the majority of individuals. Group analyses (repeated measures within-subjects analysis of variance) demonstrated significant improvement between baseline and intervention phases for the 10 metre Timed Walk (p = 0.019), MSWS-12 Scale (p = 0.041), Forward (p = 0.015) and Lateral Functional Reach (p = 0.012). These results provided preliminary scientific evidence to support the use of this intervention in ambulant individuals with MS.

The next stage is to build upon this existing evidence base by improving the methodological limitations of this pilot study. We intend to do this by undertaking an adequately powered multi-centred blinded randomised controlled study, with the *primary aim *of investigating the effectiveness of a 12 week face to face Pilates based individualised core stability training programme. Methodologically sound trials of this nature are essential to move our knowledge forwards in this area.

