#### Entry criteria

• Definite diagnosis of MS, according to McDonald's criteria [8]

• Aged 18 years or over

• Able to walk independently with or without use of intermittent or constant unilateral assistance such as walking stick or orthotic brace (4.0 - 6.5 EDSS equivalent)

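### The sample size targets a 20% change in the 10-metre walk but the primary effect is a raw difference in change; the two need one scale, and baseline adjustment would use the data better

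*Protocol article*

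**What the plan says.** In the protocol article, Sample size states that "30 people in each group is required to detect a 20% change in score on the primary outcome", "with a power = 0.85 and α = 0.05". It supports the target by saying that "A 20% change in the 10MTW has demonstrated to be clinically significant in similar samples". The source of the planning data is given as "The sample size for this study is based on data from the case series study", which Background describes as a "series of eight replicated single case studies (ABA design". No mean, SD or scale of measurement is stated.

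Analysis of primary clinical outcomes defines the treatment effect as the "difference in change (follow-up minus baseline", compared between each pair of groups and "tested and presented at the two-tailed 5% level with no adjustment of multiple testing". It promises 95% confidence intervals. It mentions no percentage, ratio, logarithm or covariate.

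Entry criteria admit anyone "Able to walk independently with or without use of intermittent or constant unilateral assistance such as walking stick or orthotic brace", which the protocol equates to EDSS 4.0 to 6.5. The 10MTW is timed once per visit.

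**The concern.** A 20% change reads naturally as a relative effect. Follow-up minus baseline is an absolute one, in seconds. The protocol gives no figure that converts one into the other, so a reader of the primary result would have a mean difference in seconds and a benchmark in per cent. As an illustration with assumed times, 20% is 0.20 × 8 = 1.6 s for a person who takes 8 s and 0.20 × 30 = 6 s for one who takes 30 s. If walking times vary widely and variability grows with time, the slowest walkers weigh most in a mean change in seconds.

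A second issue is separable from the scale. A raw change score subtracts the whole baseline value. When the baseline is a single timed walk with its own error, that error passes straight into the outcome. Regression on baseline avoids this and uses data that the trial collects anyway.

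**Working it through.** **1. The plan's own figures.** The drop-out step reproduces: 3 × 30 = 90, and 90 / (1 − 0.10) = 100. The 30 per group cannot be reproduced because no SD is given, so I solved backwards. Standardised difference = (1.960 + 1.036) × √(2/30) = 0.774, or 0.787 with the t distribution. The implied SD is therefore 20% / 0.774 = 25.9% of the mean, or 20% / 0.787 = 25.4%. With 30 per group, a 20% difference has power 97%, 73% and 49% if the SD is 20%, 30% and 40% of the mean.

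**2. Does the stated power hold for change in seconds?** This depends on what the unstated SD was.
- If it was the SD of change in seconds, and 20% meant 20% of the mean, power is about 85% as stated.
- If it was the SD of log change, 85% power needs ln(1/0.8) / 0.787 = 0.223 / 0.787 = 0.284. With proportional error entering at follow-up only, a t-test on change in seconds then has 82%, 78%, 71% and 64% power at assumed baseline CVs of 0.2, 0.4, 0.6 and 0.8.

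The document does not say which case applies.

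**3. Baseline adjustment and choice of scale.** Simulation: 30 per arm, two-sided 5%, 20,000 trials per row, lognormal true walking times, each person's true time reduced by 20% in the treated arm, independent error at both visits. Proportional error: SD of log change 0.284. Constant error: SD of change 0.254 of the mean time. The CVs and both error models are my assumptions.

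| Error | CV | Change, s | ANCOVA, s | Gain (points) | ANCOVA, log |
|---|---|---|---|---|---|
| Proportional | 0.4 | 0.74 | 0.84 | 10 | 0.88 |
| Proportional | 0.6 | 0.66 | 0.75 | 9 | 0.86 |
| Proportional | 0.8 | 0.60 | 0.68 | 8 | 0.85 |
| Constant | 0.4 | 0.83 | 0.89 | 6 | 0.72 |
| Constant | 0.6 | 0.82 | 0.86 | 5 | 0.54 |
| Constant | 0.8 | 0.79 | 0.84 | 5 | 0.40 |

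The gain in seconds runs from about 5 to 10 points here. Other reasonable calibrations of the error SD keep it within roughly 4 to 10.

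**4. Where the gain comes from.** With equal variances at both visits and baseline–follow-up correlation ρ, the residual variance of ANCOVA is (1 + ρ)/2 times that of the change score. For constant error and CV 0.4: true variance 0.4² = 0.16; error variance per visit 0.254²/2 = 0.032; ρ = 0.16 / 0.192 = 0.83; ratio 0.92. A proportional reduction adds more, because the treated arm's slope on baseline is then below 1. Two checks mark the limits. If all the error sits at follow-up, so that baseline is error-free, the gain is about nil (−1 to +2 points). If the reduction is the same number of seconds for everyone and error is constant, it is at most about 2 points.

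**5. The log scale.** Against ANCOVA in seconds, log-time ANCOVA gains 5 to 17 points under proportional error (0.88 against 0.84 at CV 0.4, 0.85 against 0.68 at CV 0.8). Under constant error it loses 17 to 43 points (0.72 against 0.89, 0.40 against 0.84). The sign depends on a property of the data that the protocol does not report.

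**The case against.** The strongest reply is that there may be no mismatch at all. The planners could have taken 20% of the pilot's mean time and the SD of change in seconds. Target and analysis would then already agree, and any influence of slow walkers would already be in the SD. This stands: nothing in the document excludes it.

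A reader might infer that the stated power is lost and that a log-time analysis restores it. The document supports neither step. It gives no SD, mean or baseline spread. Entry is limited to EDSS 4.0 to 6.5 equivalent with at most unilateral support, so a wide, right-skewed spread of times is plausible but not established. Under constant error in seconds the log analysis is clearly the weaker one.

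It can also be said that a condensed article leaves test, covariates and transformation to a full analysis plan, and that ANCOVA on the change score gives the same treatment effect as ANCOVA on follow-up. That is fair, so the absence of a model is not the point here. The article does, however, fix the effect as a difference in raw change and does state a percentage target, and it does not connect them. A difference in seconds is a valid and readable effect measure and can be expressed as a percentage of mean baseline time, but the protocol does not say that this will be done.

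**Conclusion.** The point holds in a limited form. The target is stated as a percentage without a base or scale, the primary effect is an unadjusted difference in raw change, and no figure links them. Whether 85% power is kept or lost cannot be determined from the document. Replacing the raw change score by ANCOVA on baseline is worth roughly 4 to 10 points of power for a seconds analysis under both error models. That rests on assumed CVs of 0.4 to 0.8, a true 20% reduction proportional to each person's time, 30 per arm and measurement error at both visits. The gain shrinks towards nil if baseline error is negligible, and costs almost nothing in that case. A log scale is a trade-off that needs the pilot data to settle; it is not a correction of an error. This is a clarification and a cheap improvement, not a flaw that invalidates the design.

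**What to change.** 1. In Analysis of primary clinical outcomes, replace the raw change score by ANCOVA: follow-up 10MTW as outcome, group as factor, baseline 10MTW as covariate, with the adjusted differences and 95% confidence intervals for the three comparisons.
2. In Sample size, state the pilot mean and SD, the scale of that SD, and what the 20% is a percentage of.
3. Put the target and the primary effect on one scale. Either give the target in seconds, as 20% of a stated mean, or report the effect as a ratio.
4. Pre-specify a log-time ANCOVA (log baseline as covariate), reporting a ratio with its 95% confidence interval, as a sensitivity analysis. Make it primary only if the pilot data show variability proportional to walking time, and decide this before outcome data are seen. With eight pilot cases the evidence on this will be thin, which favours the sensitivity role.

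Cost: wording only, with no extra participants or measurements. ANCOVA spends one degree of freedom. If the ratio is chosen, the result is a ratio of geometric means, which is less immediate to clinicians than seconds; a descriptive summary in seconds can accompany it.
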